### Data management

Trained staff will perform data management at each center using the Electronic Data Capture (EDC) system (https://www.mmphcrc.com/pdf/medicalHistory/vapcrf.html). The EDC system’s reliability, access control, and traceability will guarantee the quality of trial data management. Data collection will be restricted to those variables necessary to define baseline patient characteristics (demographics, VAP diagnosis, concurrent medical conditions and comorbidities, inclusion and exclusion criteria, severity of illness and organ dysfunction scores, vital signs, and laboratory results), the delivery of the nutrients, potential confounding co-interventions (life-sustaining therapies, and use of vasopressors or sedatives), and outcomes (vital signs at ICU and hospital discharge, day 28, length of stay in ICU and hospital). Randomized participants will be followed until either death or 28 days after randomization, whichever comes first. Study staff will attend follow-up by either direct contact with the patient or the next of kin. Participants who withdraw from the study will be followed up according to the follow-up schedule and analyzed on the ITT principle.

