## Methods/design

### Study design

The VIP study is designed as a prospective, multicenter, open-label, randomized, parallel-group, GTF-controlled (PTF vs. GTF 1:1) superiority trial in 4 tertiary care hospitals. The participating sites in this study include medical/surgical, medical, surgical, or emergency ICUs (see Table 1 for details of participating centers). Patient enrollment is expected to last for up to 36 months. The end of the study is defined as the last follow-up of the last enrolled patient. The trial has been registered at chictr.org.cn (ChiCTR2100051593). We used the Standard Protocol Items: Recommendations for International Trials (SPIRIT) reporting guidelines [29], and the SPIRIT checklist is attached in the Supplementary appendixes.

**Table 1 Tab1:** Research settings and names of each ethics committee

Research setting	Ethics committee name	Hospital rank and location
Maoming People’s Hospital	Medical Ethics Committee of Maoming People’s Hospital	Tertiary, Maoming, Guangdong, China
Guangdong Provincial People’s Hospital	Medical Ethics Committee of Guangdong Provincial People’s Hospital	Tertiary, Guangzhou, Guangdong, China
General Hospital of Southern Theater Command	Medical Ethics Committee of General Hospital of Southern Theater Command	Tertiary, Guangzhou, Guangdong, China
Heyuan People’s Hospital	Medical Ethics Committee of Heyuan People’s Hospital	Tertiary, Heyuan, Guangdong, China

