### Outcome measurements

Participants will be evaluated clinically and through laboratory testing according to Table 2. The following data will be recorded: demographics, VAP diagnosis, concurrent medical conditions and comorbidities, inclusion and exclusion criteria, the severity of illness and organ dysfunction scores, vital signs and laboratory results, potential confounding co-interventions (life-sustaining therapies and use of sedatives or vasopressors), and outcomes (vital status at ICU and hospital discharge, day 28 and day 90, ICU and hospital length of stay).

**Table 2 Tab2:** Trial schedule of the VIP study

Timepoint	Baseline	^**a**^Interventions									Termination
	^b^D0	D1	D2, ^c^N1	D..., N...	D4	D5	D6	D7	D8, N7	D…	D28
Eligibility screening	**×**										
Informed consent obtaining	**×**										
Randomization	**×**										
Medical history collection	**×**										
Population data collection	**×**										
Baseline data collection	**×**										
Evaluation of major adverse tube-associated events (MATE)		**×**	**×**								
Evaluation of ^d^EN related adverse events			**×**	**×**	**×**	**×**	**×**	**×**	**×**	**×**	**×**
Evaluation of serious adverse events		**×**	**×**	**×**	**×**	**×**	**×**	**×**	**×**	**×**	**×**
VAP episode		**×**	**×**	**×**	**×**	**×**	**×**	**×**	**×**	**×**	**×**
Microorganisms causing VAP		**×**	**×**	**×**	**×**	**×**	**×**	**×**	**×**	**×**	**×**
Duration of mechanical ventilation		**×**	**×**	**×**	**×**	**×**	**×**	**×**	**×**	**×**	**×**
SOFA score		**×**	**×**	**×**	**×**	**×**	**×**	**×**	**×**	**×**	**×**
CPIS score		**×**	**×**	**×**	**×**	**×**	**×**	**×**	**×**	**×**	**×**
Serum albumin and C-reactive protein		**×**	**×**						**×**		
ICU-acquired infections (bloodstream, urinary tract, catheter-related, and other infections)		**×**	**×**	**×**	**×**	**×**	**×**	**×**	**×**	**×**	**×**
Day calorie target		**×**	**×**	**×**	**×**	**×**	**×**	**×**	**×**	**×**	
Day actual calorie		**×**	**×**	**×**	**×**	**×**	**×**	**×**	**×**	**×**	
Day calorie deficit		**×**	**×**	**×**	**×**	**×**	**×**	**×**			
Ventilator free		**×**	**×**	**×**	**×**	**×**	**×**	**×**	**×**	**×**	**×**
Transfer out of ICU		**×**	**×**	**×**	**×**	**×**	**×**	**×**	**×**	**×**	**×**
ICU survival		**×**	**×**	**×**	**×**	**×**	**×**	**×**	**×**	**×**	**×**
Discharge		**×**	**×**	**×**	**×**	**×**	**×**	**×**	**×**	**×**	**×**
Hospital survival		**×**	**×**	**×**	**×**	**×**	**×**	**×**	**×**	**×**	**×**

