28-day survival											**×**

Eligibility screening includes diagnosis, inclusion/exclusion criteria, urine pregnancy test for female, demographics, medical history, and physical examination

*CPIS* Clinical Pulmonary Infection Score, *EN* Eenteral nutrition, *MATE* Major adverse tube-associated event, *SOFA* Sequential Organ Failure Assessment score

^a^Intervention means postpyloric tube feeding

^b^D means day from enrollment

^c^N means day from enteral nutrion

^d^EN-related adverse events include abdominal distension, gastric retention, vomiting, diarrhea, and aspiration of gastric contents

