#### Data analysis

All analyses will be performed according to the ITT principle. A *P* value < 0.05 is considered statistically significant. All tests are two-sided with no adjustment for multiple comparisons. Continuous variables are reported as means and standard deviations or medians and interquartile ranges. Categorical variables are reported as proportions. Pearson’s chi-squared test and adjusted multivariable analysis will be applied for the primary outcome. We plan to perform subgroup analyses for the primary outcome for predefined variables: the proportion of patients with at least 1 VAP episode. All the other data, including age, gender, body mass index (weight, height), SOFA score, primary admission diagnosis, coexisting illness, and type of admission, will be presented as descriptive results. Pearson’s chi-squared test will compare incidence or mortality outcomes between groups. The *t*-test will compare total VAP episodes, SOFA scores, time to VAP onset from mechanical ventilation, mechanical ventilation duration, ICU and hospital lengths of stay, inflammatory biomarkers, and function indicators between groups. A paired *t*-test or repeated measures ANOVA will be used to compare baseline and changes during the intervention.

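### Follow-up ends at day 28, but the ICU and hospital outcomes carry no day-28 limit and one data list asks for day-90 vital status

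*Protocol article*

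**What the plan says.** The follow-up rule in Data management has no exception: "Randomized participants will be followed until either death or 28 days after randomization, whichever comes first". Table 2 agrees. Its final column is the termination visit on D28, discharge and hospital survival are tracked only to that column, and its last survival item is "28-day survival".

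Other sections ask for more. Outcome measurements lists, as data to be recorded, "vital status at ICU and hospital discharge, day 28 and day 90, ICU and hospital length of stay". Secondary efficacy endpoints names ICU, hospital and day-28 mortality, ventilation duration, and ICU and hospital stay. In that list only ventilator-free days and one of the three mortality rates are tied to day 28.

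A second data list, in Data management itself, reads "outcomes (vital signs at ICU and hospital discharge, day 28, length of stay in ICU and hospital". It omits day 90 and has vital signs where the other list has vital status.

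Data analysis assigns Pearson's chi-squared test to mortality, and the t-test to a group of variables that includes "time to VAP onset from mechanical ventilation, mechanical ventilation duration, ICU and hospital lengths of stay". Study design says "The end of the study is defined as the last follow-up of the last enrolled patient", which adds no later visit.

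**The concern.** Mortality, ventilation days, ICU or hospital stay and cost of care are the stated secondary objectives, and several of the endpoints serving them are complete only once the patient has left the ventilator, the ICU or the hospital. A rule that closes follow-up at day 28 leaves these open for exactly the longest-staying patients, so the incompleteness is not random. If postpyloric feeding changes stay or survival, the share of incomplete patients will also differ between arms. Neither planned test has a place for a censored value, so someone must choose how to code these patients, and that choice affects the comparison. Day-90 status fails more broadly: it would be lacking for every patient alive at day 28, including those already home.

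**Working it through.** The plan gives no figure to reproduce here, so the check compares the sections with one another.

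**What is known at day 28, by patient state, under the stated rule**

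- Died by day 28: all mortality outcomes and durations are known.
- Discharged alive by day 28: discharge status and both stays are known; day-90 status is not.
- In hospital but out of the ICU and off the ventilator: hospital mortality, hospital stay and day-90 status are open.
- In the ICU but off the ventilator: ICU mortality and ICU stay are open as well.
- Still ventilated: ventilation duration is open too.

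Three outcomes are complete in every one of these states: day-28 mortality, ventilator-free days to day 28, and VAP as scheduled in Table 2 through D28. The conflict does not reach them.

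**What the planned tests would do with open cases**

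- Chi-squared test of hospital mortality: an inpatient at day 28 is counted as alive or excluded.
- t-test of stay: the value is set to the time reached at day 28, or the patient is excluded.

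The article does not say which.

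**Illustration of capping (assumed inputs, none from the documents)**

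Let hospital stay from randomization be lognormal with median m and log-SD s, ignoring death. Then:

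- Share beyond day 28 = 1 − Φ(ln(28/m)/s)
- Mean = m·exp(s²/2)
- Mean capped at 28 = mean·Φ((ln(28/m) − s²)/s) + 28·[1 − Φ(ln(28/m)/s)]

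Mild end, m = 14 and s = 0.7:

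- ln(28/14)/0.7 = 0.99, so 16% of stays pass day 28.
- Mean = 14·exp(0.245) = 17.9 days; capped mean 15.5 days.
- A true 15% shortening in one arm is 0.15 × 17.9 = 2.7 days; after capping it is 1.8 days.

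Severe end, m = 28 and s = 0.9:

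- ln(28/28)/0.9 = 0, so 50% of stays pass day 28.
- Mean = 28·exp(0.405) = 42.0 days; capped mean 21.7 days.
- A true 15% shortening is 0.15 × 42.0 = 6.3 days; after capping it is 1.3 days.

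Under these assumptions capping pulls the stay comparison towards no difference. How far depends on a distribution that the documents do not supply.

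**The case against.** The best defence is that day 28 ends only contact with the patient or next of kin, and that discharge dates and status come from site records. Data management lists discharge outcomes and stay just before the 28-day sentence, which fits that reading. Another reading is that Table 2 makes all these outcomes 28-day quantities. Either may be intended, so a reader who infers that the data will certainly be lost goes further than the text allows. But neither reading is stated, and the limit is written without exception. The endpoint list also ties ventilator-free days to day 28 and names hospital mortality separately from day-28 mortality. That suggests, without proving, that the hospital outcomes were meant to run on.

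A second defence is that handling rules belong in a statistical analysis plan or full protocol, which are not shown. This holds for the coding of open cases, and their absence from the article is not the point made here. An analysis plan cannot, however, supply data that the follow-up rule stops collecting, nor settle day 90 in one section against day 28 in another.

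A reader might also infer that the planned tests cannot be run on these patients. They can: death in hospital by day 28 and a capped stay are both computable. They answer a different question from the endpoints as named.

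Finally, day 90 appears once, in a data list; no endpoint, objective or test uses it, and it may be a leftover phrase. That stands. No named endpoint is lost through day 90, and the conflict over ICU and hospital outcomes does not depend on it.

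**Conclusion.** The sections contradict one another. Data management and Table 2 close follow-up at day 28, while the secondary endpoints include ICU and hospital outcomes with no such limit, and Outcome measurements adds a day-90 status that the stated follow-up cannot deliver. The matter should be corrected, but it is confined to secondary outcomes, and day-28 mortality and ventilator-free days still give usable answers on mortality and ventilation.

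No size can be derived from the documents. One could take 20% still in hospital at day 28 with a quarter of them dying later, and conclude that hospital mortality is understated by 0.20 × 0.25 = 5 percentage points. The documents do not support that. Both inputs are assumptions, the result holds only if inpatients are counted as survivors, and it concerns the absolute rate, not the difference between arms. The capping figures in the working likewise show a direction and a range under assumed distributions, not an estimate for this trial.

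**What to change.** Reconcile Outcome measurements, Table 2, Secondary efficacy endpoints and Data management in one of two ways.

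(a) State that discharge dates and vital status at discharge are taken from site records after day 28 until ICU and hospital discharge, up to a stated cap, and extend Table 2 to match. Then either delete day 90 or add a day-90 contact for every patient alive at day 28. Following patients to discharge alone would not yield day-90 status for those discharged earlier. The cost is a record check for each patient still in hospital at day 28 and, if day 90 is kept, one contact per day-28 survivor.

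(b) Delete day 90. Redefine the mortality endpoints as ICU death and in-hospital death by day 28, and the durations and stays as censored at day 28. Replace the plain t-test for those durations with a method that handles censoring and death. This costs only wording and a little analysis work.

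Under either route, use vital status in both data lists if that is what is meant. Make the choice before outcomes are examined by arm, so that it cannot look driven by the results.

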### Data monitoring committee

A Data Monitoring Committee (DMC) will be responsible for data monitoring and blinded analysis. Members of the committee are experts in medicine, biometric statistics, and medical ethics who are independent and have no competing interests in the trial. No interim analysis is planned for this trial. The DMC will audit the trial regularly and advise the Research Ethics Committee in each center, who will also audit and determine to continue, modify, or discontinue the trial.

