### Adverse events and serious adverse events

All treatment-related adverse events (AEs) and serious adverse events (SAEs) should be recorded on eCRF. SAEs will be reported to the Institutional Ethics Committee within 24 h of study staff becoming aware of the events. The participants are provided with commercial clinical research insurance by the manufacturer of the study product. Determination criteria for AE and SAE are detailed in Supplementary Appendix 5.

The treating physician will be responsible for determining the causal relationship of the SAE as either definitely, possibly, possibly not, or definitely not study treatment-related, as well as unclassified.

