#### Interim analysis

No interim analysis is planned for this trial.

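### The plan makes the DMC's analysis blinded and leaves stopping to four centre ethics committees, and it describes no point during the trial at which harm by arm, pooled over centres, reaches any of them

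*Protocol article*

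**What the plan says.** All of this is in the protocol article.

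- **Data monitoring committee.** "A Data Monitoring Committee (DMC) will be responsible for data monitoring and blinded analysis". Members are independent and include statistical expertise. The committee audits regularly, but its output is advice. It is to "advise the Research Ethics Committee in each center, who will also audit and determine to continue, modify, or discontinue the trial".
- **Interim analysis** (and again in the DMC section). "No interim analysis is planned for this trial".
- **Adverse events and serious adverse events.** "SAEs will be reported to the Institutional Ethics Committee within 24 h of study staff becoming aware of the events". The same section also requires a data entry: "All treatment-related adverse events (AEs) and serious adverse events (SAEs) should be recorded on eCRF". On causality: "The treating physician will be responsible for determining the causal relationship of the SAE".
- **Study design and Table 1.** The trial is open-label, a "GTF-controlled (PTF vs. GTF 1:1) superiority trial in 4 tertiary care hospitals". Table 1 lists a separate ethics committee for each hospital.
- **Objectives.** Safety of postpyloric feeding is a primary objective alongside efficacy.

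**The concern.** The DMC is the one independent body described as looking across all sites, and the only analysis assigned to it is blinded. The power to stop lies elsewhere, with four local committees, and no lead committee or rule for disagreement is given. The SAE section names the ethics committee as recipient and does not mention the DMC.

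The arms differ in procedural risk. Controls have a nasogastric tube placed by nurses. The postpyloric group undergoes narcosis and gastroscopy (Endoscopic feeding tube placement), and patients are enrolled within 6 h of intubation (Inclusion criteria). The listed harms include thoracic misplacement, bleeding and perforation (Safety endpoints).

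Deaths and serious events are common in ventilated ICU patients whichever tube they have, so a moderate excess is hard to recognise case by case. It shows when the arms are compared. The Trial status section has recruitment running from December 2021 to about July 2025, a long time to go without a described comparison. Site staff already know the allocation, so blinding the DMC does little against bias at the bedside.

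**Working it through.** **Step 1. Who is described as seeing what during the trial.**

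| Body | Role in stopping | Safety information described |
|---|---|---|
| DMC | Advises | Data monitoring, regular audit, blinded analysis; SAEs are on the eCRF, but no by-arm table is described |
| Four centre ethics committees | Decide | SAE reports to the Institutional Ethics Committee within 24 h, plus the DMC's advice; no pooled by-arm table is described |
| Treating physicians | None stated | Own patients, allocation known; rate causality |

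No row combines harm by arm, all four centres, and a role in stopping.

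**Step 2. What a pooled view shows and what it hides.** The plan gives no figure on this point to reproduce, so the following is illustration only.

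Inputs: 924 patients in total (Sample size estimation), so half-way is 924/2 = 462, or 231 per arm. Control mortality is assumed at 25% to 34.5%, and mortality is assumed 10 points higher with postpyloric feeding. The documents support neither assumption. The 34.5% in the Background is mortality with VAP, not mortality of all ventilated patients.

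By-arm comparison: z = d / √[(p₁(1−p₁) + p₂(1−p₂))/231].
- 25% vs 35%: √[(0.1875 + 0.2275)/231] = 0.0424; z = 0.10/0.0424 = 2.36.
- 34.5% vs 44.5%: √[(0.2260 + 0.2470)/231] = 0.0452; z = 0.10/0.0452 = 2.21.

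Pooled view: with 1:1 allocation the pooled rate is p₁ + d/2, so a 10-point excess moves it by 5 points.
- 30.0%: SE = √(0.30 × 0.70/462) = 2.1 points.
- 39.5%: SE = √(0.395 × 0.605/462) = 2.3 points.

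A 5-point shift is also a little over two SEs, so random error is not the obstacle. The obstacle is that the shift can be read only against a known expected rate. The protocol states none, and the assumed control range alone is 34.5 − 25 = 9.5 points wide. A pooled figure also cannot say which arm carries the excess. A by-arm table needs no outside rate.

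**Step 3. A rare event.** Six events, all in one arm of 231 and none in the other, give a two-sided Fisher P of 0.030. Spread over four centres, that is 6/4 = 1.5 cases per ethics committee on average.

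**Step 4. A smaller excess.** At 8 points, with control mortality of 20% to 34.5%, the two-sided 5% comparison at 231 per arm has 52% to 42% power, and at 462 per arm 81% to 71%. By-arm review would often miss such an excess half-way.

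**The case against.** The strongest reply is that the text forbids very little. Four parts of it stand.

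- A reader might infer that SAEs go only to the ethics committees. The article does not say so. SAEs are also entered on the eCRF, and the DMC is charged with monitoring data. Onward SAE routing is the kind of detail an article may leave to the full protocol or a DMC charter.
- A reader might infer that no body able to stop the trial ever learns of harm by arm. That goes too far. The ethics committees receive individual SAEs from an open-label trial in which causality is rated, so they may know the arm of a single case. Perforation or thoracic misplacement can be recognised case by case, which weakens the rare-event example.
- The article does not define what is blinded in the DMC's analysis. If it means arms coded A and B, the DMC could see an imbalance before the end. The plan therefore does not establish that an imbalance would stay hidden until the final analysis.
- It is speculation that one centre would stop while another continued on the same signal. One DMC advises all the committees, and the decision is worded as concerning the trial as a whole.

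The reply does not remove the stated choices: a blinded analysis for the DMC, no interim analysis, and a stopping decision placed in each centre. A charter that provided by-arm safety review would have to be reconciled with the article's description of the DMC.

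**Conclusion.** The point holds as a gap in what the plan describes. It is not proof that harm would go unseen. As written, no comparison of harm by arm, pooled over centres, is described as reaching the DMC or the committees that can stop the trial. This matters because safety is a primary objective and one arm carries an added endoscopic procedure.

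Its size cannot be taken from the documents. The 10-point excess and the control rates of 25% to 34.5% are assumptions for illustration. On them, a half-way comparison gives z of 2.2 to 2.4, while the pooled rate moves 5 points with no stated expected rate and no indication of the arm. With an 8-point excess the same look has only about even power. The conclusion rests on the article's wording; a coded-arm reading of the blinding, once stated, would narrow it to SAE routing and coordination between committees. The change is worth making because it is cheap.

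**What to change.** 1. **Data monitoring committee section.** Replace the blinded analysis with periodic closed-session review of deaths, SAEs and MATEs, tabulated by arm over all sites from the existing EDC system and prepared by the DMC's own statistical member. State whether arms are coded or unmasked.
2. **Same section.** Have the DMC issue one trial-wide recommendation, sent to all four ethics committees at the same time.
3. **Same section and Interim analysis section.** Reword to say that no interim efficacy analysis is planned. Because 28-day, ICU and hospital mortality are also secondary efficacy endpoints, add that deaths are reviewed for harm only and that VAP is not compared. The alpha for the primary endpoint is then unaffected.
4. **Adverse events and serious adverse events section.** Reconcile the SAE route with the DMC's role so that the DMC also receives SAEs.

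The cost is a few safety tables and wording in three sections, with no extra patients. The small downside is that DMC members see results by arm, which calls for confidentiality of the closed session.
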